## Abstract

**Background:**

Damage control laparotomy, or abbreviated initial laparotomy followed by temporary abdominal closure (TAC), intensive care unit resuscitation, and planned re-laparotomy, is frequently used to manage intra-abdominal bleeding and contamination among critically ill or injured adults. Animal data suggest that TAC techniques that employ negative pressure to the peritoneal cavity may reduce the systemic inflammatory response and associated organ injury. The primary objective of this study is to determine if use of a TAC dressing that affords active negative pressure peritoneal therapy, the ABThera Open Abdomen Negative Pressure Therapy System, reduces the extent of the systemic inflammatory response after damage control laparotomy for intra-abdominal sepsis or injury as compared to a commonly used TAC method that provides potentially less efficient peritoneal negative pressure, the Barker’s vacuum pack.

**Methods/Design:**

The Intra-peritoneal Vacuum Trial will be a single-center, randomized controlled trial. Adults will be intraoperatively allocated to TAC with either the ABThera or Barker’s vacuum pack after the decision has been made by the attending surgeon to perform a damage control laparotomy. The study will use variable block size randomization. On study days 1, 2, 3, 7, and 28, blood will be collected. Whenever possible, peritoneal fluid will also be collected at these time points from the patient’s abdomen or TAC device. Luminex technology will be used to quantify the concentrations of 65 mediators relevant to the inflammatory response in peritoneal fluid and plasma. The primary endpoint is the difference in the plasma concentration of the pro-inflammatory cytokine IL-6 at 24 and 48 h after TAC dressing application. Secondary endpoints include the differential effects of these dressings on the systemic concentration of other pro-inflammatory cytokines, collective peritoneal and systemic inflammatory mediator profiles, postoperative fluid balance, intra-abdominal pressure, and several patient-important outcomes, including organ dysfunction measures and mortality.

**Discussion:**

Results from this study will improve understanding of the effect of active negative pressure peritoneal therapy after damage control laparotomy on the inflammatory response. It will also gather necessary pilot information needed to inform design of a multicenter trial comparing clinical outcomes among patients randomized to TAC with the ABThera *versus* Barker’s vacuum pack.

**Trial registration:**

ClinicalTrials.gov identifier
http://www.clicaltrials.gov/ct2/show/NCT01355094

## Background

Intra-abdominal sepsis and abdominal trauma constitute major international public health problems
[1]. As limited treatments aside from source control and antimicrobial therapy exist for severe intra-abdominal infections, intra-peritoneal sepsis is associated with significant morbidity and mortality
[2]. Moreover, trauma affects approximately 700 million people, including 30 million North Americans and 2 million Canadians, worldwide each year
[1,3]. These injuries result in 5 million deaths, with blunt and penetrating abdominal trauma constituting a substantial proportion of trauma-related mortality
[1,3,4].

Deranged patient physiology as a result of massive hemorrhage and/or contamination from hollow viscus or pancreaticobiliary injuries is an important contributor to poor outcomes after intra-abdominal sepsis or injury
[5,6]. In an attempt to limit this deranged physiology, damage control laparotomy, or abbreviated initial laparotomy followed by temporary abdominal closure (TAC) and planned re-operation after intensive care unit (ICU) resuscitation, is increasingly used to manage intra-abdominal bleeding and contamination among these patients
[5-10]. The stages of damage control laparotomy broadly include: (1) limited initial operation with temporary control of hemorrhage and contamination; (2) application of a TAC device; (3) ICU resuscitation; and (4) re-operation with attempted completion of definitive surgical repairs after normalization of patient physiology
[5,7-9].

A common component of the deranged physiologic response after intra-abdominal sepsis or injury is inflammation. Although intra-abdominal sepsis or injury also results in a systematic inflammatory response, evidence suggests that this response is exaggerated in the peritoneum
[11,12]. Microcirculatory disruption after septic or hemorrhagic shock may lead to loss of intestinal barrier function, bowel edema, and formation of pro-inflammatory-mediator-rich ascites
[13-18]. This inflammatory ascites may serve as a motor for sepsis, which may perpetuate systemic inflammation and result in multi-organ dysfunction syndrome
[11,12,14,18]. In support of this, the levels of select peritoneal cytokines have been reported to be significantly different between animals that survived as compared to those who died in animal models of intra-abdominal sepsis
[19]. However, although a number of mediators have been associated with sepsis or injury, relatively little is known about their temporal peritoneal and systemic expression after intra-abdominal sepsis or injury, including abdominal surgery (Table 
1)
[16,20-43].

**Table 1 T1:** Inflammatory mediators associated with intra-abdominal sepsis or injury, including abdominal surgery, among studies of animals or humans

**Mediator**	**Potential role in intra-abdominal sepsis or injury**	**Reference(s)**
CRP	A serum marker of sepsis that increases in concentration in plasma following abdominal surgery	[20-22]
Haptoglobulin	Elevated expression in blood leukocytes following severe blunt trauma	[23]
IL-1ra	Elevated in plasma following trauma; elevated expression in blood leukocytes following severe blunt trauma	[23,24]
IL-6	Potent inflammatory mediator and marker of sepsis; elevated levels correlate with length of hospital stay, complications, and mortality among patients with intra-abdominal sepsis; elevated levels in peritoneal fluid in a porcine model of intra-abdominal sepsis; elevated plasma/serum levels following abdominal surgery; elevated plasma levels following severe trauma associate with injury severity, development of organ dysfunction, and poor outcomes, including mortality	[21-23,25-28,44-50]
IL-8	Potent neutrophil chemoattractant; elevated expression in blood leukocytes following severe blunt trauma	[23,29]
IL-10	Elevated serum levels during intra-abdominal sepsis; blocks pro-inflammatory cytokine release; elevated after abdominal surgery	[30-32]
IL-15	Elevated levels in serum correlate with organ dysfunction and poor patient prognosis	[33]
IL-17	Potent pro-inflammatory mediator; promotes neutrophil recruitment to the peritoneal cavity and enhanced bacterial clearance in a mouse model of intra-abdominal sepsis; elevated plasma levels in select patients following severe trauma	[28,34,35]
IL-22	Elevated serum levels during intra-abdominal sepsis	[30]
IL-33	Mediates neutrophil recruitment to peritoneum; promotes bacterial clearance and reduces mortality in a mouse model of intra-abdominal sepsis	[36]
MCP-1 (CCL2)	Potent monocyte chemoattractant; serum levels elevated in a rat model of intra-abdominal sepsis; elevated expression in blood leukocytes following severe blunt trauma	[23,37]
M-CSF	Elevated in plasma following trauma	[24]
MIF	Present early in sepsis and remains elevated for a prolonged time period; significantly higher levels in non-survivors of sepsis compared to survivors; MIF neutralization reduces mortality in a mouse model of intra-abdominal sepsis	[38,39]
PDGF	Elevated in plasma following trauma	[24]
Procalcitonin	Marker of infectious complications following abdominal surgery and negatively associated with survival; elevated after abdominal surgery	[32,40]
TNF-α	Serum levels elevated in a rat model of intra-abdominal sepsis	[37]
tPA	Enhances bacterial clearance, reduces cellular influx, increases plasma and peritoneal IL-12 and IL-10 levels, and reduces lung and liver damage in a mouse model of intra-abdominal sepsis	[16]
TRAIL	Promotes inflammatory cell recruitment to the peritoneum, enhances bacterial clearance, and reduces mortality in a mouse model of intra-abdominal sepsis; modulates apoptosis	[41,42]

CCL2, Chemokine (C-C motif) ligand 2; CRP, C-reactive protein; IL-1ra, Interleukin-1 receptor antagonist; IL-6, Interleukin-6; IL-8, Interleukin-8; IL-10, Interleukin-10; IL-15, Interleukin-15; IL-17, Interleukin-17; IL-22, Interleukin-22; IL-33, Interleukin-33; MCP-1, Monocyte chemoattractant protein-1; M-CSF, Macrophage colony-stimulating factor; MIF, Macrophage migration inhibitory factor; PDGF, Platelet-derived growth factor; TNF-α, Tumor necrosis factor-alpha; tPA, Tissue plasminogen activator; TRAIL, Tumor necrosis factor-related apoptosis-inducing ligand.

Importantly, animal data suggest that TAC techniques that employ constant negative pressure to the peritoneal cavity may remove inflammatory ascites, reduce the systemic inflammatory response, and improve organ injury and potentially outcomes
[10,18]. One preclinical study randomly allocated animals with intra-abdominal sepsis to TAC with vacuum-assisted drainage of the peritoneal cavity after laparotomy and observed significantly reduced levels of the pro-inflammatory cytokines tumor necrosis factor-α (TNF-α) and interleukin (IL)-1β, -6, and −12 as compared to those who received a TAC that afforded only passive peritoneal drainage
[18]. Animals with septic open abdominal wounds treated with negative pressure peritoneal therapy also demonstrated significantly reduced intestinal edema and improved pulmonary, renal, and hepatic histological features; intra-abdominal pressure (IAP); cardiac and renal function; and pulmonary compliance, with a trend towards a lower incidence of acute lung injury
[18]. These animal data are interesting as several studies have reported that the pro-inflammatory cytokine IL-6 is associated with an increased risk of organ dysfunction, adverse complications, and/or mortality among trauma victims and patients with sepsis
[44-50].

However, very little relevant clinical data yet exist to support that negative pressure peritoneal therapy may improve outcomes among trauma and acute care surgery patients after damage control laparotomy
[10]. One systematic review and meta-analysis of largely uncontrolled case series of damage control laparotomy suggested that vacuum-assisted TAC techniques may be associated with improved outcomes among critically ill adults with contaminated open abdominal wounds
[51]. However, a systematic review conducted by our group in 2012 found only 11 comparative studies, including 2 randomized controlled trials (RCTs) and 9 cohort studies, examining the efficacy and safety of negative pressure peritoneal therapy *versus* alternate TAC methods among critically ill or injured adults
[10]. As only one RCT compared negative pressure peritoneal therapy with an alternate type of TAC technique
[52], and all studies were associated with at least a moderate risk of bias and significant clinical heterogeneity, we concluded that there was insufficient evidence to support the preferential use of negative pressure peritoneal therapy after damage control laparotomy
[10].

The primary objective of this study is to determine if use of a TAC dressing that may afford active negative pressure peritoneal therapy, the ABThera™ Open Abdomen Negative Pressure Therapy System (Kinetic Concepts Inc. (KCI), San Antonio, TX, USA)
[10,53], reduces the extent of the systemic inflammatory response after damage control laparotomy for intra-abdominal sepsis or injury as compared to a commonly used TAC method that provides potentially less efficient peritoneal negative pressure, the Barker’s vacuum pack
[54-56].

## Methods/Design

### Overview

The Intra-peritoneal Vacuum Trial is a single-center RCT, which will intraoperatively allocate critically ill or injured adults to TAC with either the ABThera™ or Barker’s vacuum pack after damage control laparotomy for intra-abdominal sepsis or injury. Although the trial in itself may not be sufficient to establish superiority of the ABThera™ over the Barker’s vacuum pack, we hypothesize superiority, and will examine for evidence of this in hypothesis tests. The CONSORT flow diagram
[57] and an overview of the study design are presented in Figures 
1 and
2, respectively.

**Figure 1 F1:**
[figure not shown]
**Flow of participants in the Intra-peritoneal Vacuum Trial.** Diagram constructed according to the CONSORT statement
[57].

**Figure 2 F2:**
[figure not shown]
**Overview of the design of the Intra-peritoneal Vacuum Trial.** Where per-protocol treatment will be defined as the allocated temporary abdominal closure dressing having been in place for at least 24 h. ICU, intensive care unit; IL-6, interleukin-6; h, hours; NPT, negative pressure therapy.

### Intervention and comparator choice rationale

The ABThera™ was chosen as the intervention as its design may allow for active, and potentially equally distributed vacuum pressures throughout the peritoneal cavity and across the viscera
[58], theoretically enabling effective removal of pro-inflammatory-mediator-rich intra-peritoneal fluid. The Barker’s vacuum pack was chosen as the comparator as it is a commonly used TAC technique, which has been recommended by the Eastern Association for the Surgery of Trauma as the current standard by which to measure other devices
[59].

### Setting

The trial will be set at the Foothills Medical Centre (FMC) in Calgary, Alberta, Canada. The FMC is a University of Calgary-affiliated, adult, tertiary care, level one regional trauma center that affords trauma and emergency general surgical services for southern Alberta, southwest British Columbia, and southeast Saskatchewan. Postoperative critically ill or injured adults at the FMC are cared for in a 30-bed, closed, medical/surgical/neurosurgical ICU staffed by fellowship-trained intensivists.

### Patient recruitment

Recruitment into the trial will occur in the operating room once the decision has been made by the attending trauma or general surgeon to perform a damage control laparotomy and TAC. We will define an open abdomen as that requiring a TAC due to the abdominal skin and fascia not being closed after laparotomy.

Although no objective, evidence-based indications for damage control laparotomy or open abdominal management exist
[60,61], the Eastern Association for the Surgery of Trauma suggest that this technique may be considered in cases of severe abdominal trauma involving hepatic, non-hepatic, or vascular injuries with intra-abdominal packing; among trauma patients with acidosis (pH ≤7.2), hypothermia (temperature ≤35°C), and clinical coagulopathy or if the patient is receiving massive transfusion; and in patients with severe intra-abdominal infection/peritonitis or necrotizing pancreatitis
[59]. Other indications for the procedure suggested in 2005 by a multidisciplinary expert advisory panel on management of the open abdomen included bowel edema and a significant risk of developing abdominal compartment syndrome
[62].

### Inclusion criteria

•Age ≥18 years

•Decision made by the attending trauma or general surgeon to perform a damage control laparotomy with application of a TAC device during the index laparotomy

•Requirement for postoperative ICU admission

### Exclusion criteria

•Age <18 years

•Decision made to perform a definitive or single-stage laparotomy with closure of the abdominal fascia during the index laparotomy

•Administration of intraperitoneal chemotherapy for treatment of intra-abdominal malignancies

•Pregnancy

### Eligible, non-randomized patients

Dedicated research coordinators will screen all ICU admissions daily and identify and record patients admitted with an open abdominal wound. When potentially eligible patients are identified that were not recruited, the principal investigator, a trauma and acute care surgeon ([name]), will be informed such that he can ascertain and record reason(s) why these patients were not randomized. These reasons and the list of eligible, non-randomized patients will be used to populate the CONSORT flow diagram and estimate trial feasibility (see below).

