### Patient randomization

To preserve allocation concealment, randomization will be performed using a random treatment generator hosted on a dedicated, publicly available trial website (http://www.peritonealvac.com/). When an eligible patient is identified by the attending surgeon, this website will be accessed by a member of the operating room team and the patient’s last name and hospital number will be entered. The random treatment allocation will then be announced such that the attending surgeon can perform the indicated method of TAC. Variable block size randomization will be performed to ensure equal numbers of patients in each treatment group. Day 1 is considered the day of randomization.

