#### Secondary endpoints and exploration of clinical efficacy and safety

Secondary endpoints of interest include trial feasibility (number of patients enrolled/number of eligible candidates) and the differential effects of the allocated TAC dressings on several physiological and organ dysfunction outcomes, including: (1) the plasma concentration of TNF-α and IL-1, -8, -10, and −12 at 24 and 48 h; (2) the collective peritoneal and systemic mediator profiles (see below); (3) the activation potential of peritoneal fluid
[70,71]; (4) peritoneal fluid drainage volume; (5) postoperative daily fluid balance; (6) SOFA scores and individual organ system components of these scores; (7) the PaO_2_/FIO_2_ ratio; (8) vasopressor requirements and arterial lactate levels; (9) need for renal replacement therapy; (10) RIFLE criteria; (11) APACHE-II scores; and (12) 24 h enteral tolerance (if no gastrointestinal anastomosis was performed).

Secondary clinical efficacy and safety endpoints of interest include: (1) in-hospital death; (2) fascial closure rate and days with fascial closure for the month after admission to hospital; (3) ventilator-free days for the month after admission to hospital; (4) ICU-free days from the month after admission to hospital; (5) hospital-free days from the month after admission to hospital; and (6) risk of renal replacement therapy and days free of renal replacement therapy from the month after admission to hospital. Further, as some have suggested that negative pressure peritoneal therapy may be associated with an increased risk of abdominal fistula formation or development of intra-abdominal hypertension/recurrent abdominal compartment syndrome
[72-74], additional safety outcomes include: (1) intestinal and enteroatmospheric fistula formation; (2) daily IAP; (3) daily WSACS intra-abdominal hypertension grading classification; and (4) risk of abdominal compartment syndrome development.

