### Sample size

No clinical data yet exist on the effect of negative pressure peritoneal therapy on the inflammatory response after damage control laparotomy for intra-abdominal sepsis or injury. Thus, estimates are not available to allow accurate sample size estimation. We therefore propose to undertake a study among a convenience sample of 46 adults. As there are approximately 40 to 50 patients who undergo damage control laparotomy and open abdominal management per year at our institution, this trial should be able to be completed within a 2-year time period.

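### The feasibility denominator is built from ICU admissions although eligibility is fixed in the operating room, so eligible, non-enrolled patients who die before reaching the ICU are missed and the ratio can only err upward

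*Protocol article*

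**What the plan says.** Four parts of the protocol article bear on this.

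- **Where patients enter.** Under Patient recruitment: "Recruitment into the trial will occur in the operating room once the decision has been made by the attending trauma or general surgeon". Under Patient randomization: "When an eligible patient is identified by the attending surgeon, this website will be accessed by a member of the operating room team". Enrolment is thus complete, and recorded on the website, before the patient leaves the operating room.
- **Who is eligible.** Besides age, the Inclusion criteria list two conditions: "Decision made by the attending trauma or general surgeon to perform a damage control laparotomy with application of a TAC device during the index laparotomy" and "Requirement for postoperative ICU admission". The second is a need judged during surgery. It does not say that the patient must reach the ICU.
- **How eligible but non-randomised patients are found.** Under Eligible, non-randomized patients: "Dedicated research coordinators will screen all ICU admissions daily and identify and record patients admitted with an open abdominal wound". The principal investigator then records why each was not randomised. According to the same section, the reasons and "the list of eligible, non-randomized patients will be used to populate the CONSORT flow diagram and estimate trial feasibility". No other source of candidates is named.
- **What the count is for.** The secondary endpoints include "trial feasibility (number of patients enrolled/number of eligible candidates"). The Discussion makes pilot information on feasibility a secondary aim, intended to inform a multicentre trial.

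**The concern.** The numerator is recorded in the operating room. The non-enrolled part of the denominator is collected later, among people who survived to ICU admission. A death in the interval between the two removes a non-enrolled candidate from the count but leaves an enrolled patient in it. The omission is one-sided, so it does not average out.

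The stake is limited but real. The ratio is a stated secondary endpoint and would feed recruitment planning for the later trial, and the same list fills the screening part of the CONSORT diagram. The Discussion also notes that these operations are often done at night, when research coordinators are not available, so capture by a coordinator in the operating room cannot be presumed.

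**Working it through.** The article states no feasibility ratio, target or threshold, so there is no figure to reproduce. The check has two parts: direction by algebra, and size under stated assumptions.

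**Direction.** Let R be the randomised patients, S the eligible non-randomised patients seen in the ICU screen, and M the eligible non-randomised patients who never reach the ICU.

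- Reported ratio = R / (R + S)
- True ratio = R / (R + S + M)

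The reported ratio exceeds the true one whenever M > 0 and equals it when M = 0. It cannot fall below it through this mechanism.

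**Inputs for size.**

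- R = 46. Sample size section: "We therefore propose to undertake a study among a convenience sample of 46 adults".
- Truly eligible, T = 80 to 100. The same section gives about 40 to 50 damage control laparotomies with open abdominal management per year at the institution and a 2-year period: 2 × 40 = 80 and 2 × 50 = 100. Treating all of these as eligible is an assumption.
- m = the share of eligible non-enrolled patients who die before ICU arrival. The documents give no value; the range 0 to 20% is an assumption.

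**Formula.** M = m × (T − R). Reported ratio = R / (T − M). Overstatement = R / (T − M) − R / T.

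**Worked case, T = 90.** Non-enrolled = 90 − 46 = 44. True ratio = 46 / 90 = 51.1%.

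- m = 5%: M = 2.2; reported 46 / 87.8 = 52.4%; overstatement 1.3 points.
- m = 10%: M = 4.4; reported 46 / 85.6 = 53.7%; overstatement 2.6 points.
- m = 20%: M = 8.8; reported 46 / 81.2 = 56.7%; overstatement 5.5 points (from unrounded values).

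**Across the range of T.**

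| Truly eligible | True ratio | Reported, m = 0 | m = 5% | m = 10% | m = 20% | Largest overstatement |
|---|---|---|---|---|---|---|
| 80 | 57.5% | 57.5% | 58.7% | 60.1% | 62.8% | 5.3 points |
| 90 | 51.1% | 51.1% | 52.4% | 53.7% | 56.7% | 5.5 points |
| 100 | 46.0% | 46.0% | 47.3% | 48.6% | 51.6% | 5.6 points |

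The size depends mainly on m and hardly at all on T within this range. One missed patient out of 90 moves the ratio from 51.1% to 46 / 89 = 51.7%.

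**The case against.** The strongest reply is that the gap is narrow by the trial's own criteria. Eligibility needs a temporary closure device applied at the index operation and a requirement for ICU care. Someone who dies on the table before the dressing is applied arguably never qualifies. What remains is mainly patients who leave surgery with an open abdomen, bound for the ICU, not enrolled, and who die on the way. Screening ICU admissions for an open abdomen tracks that population closely, and nothing in the documents shows that such deaths are common. This stands as a limit on size. It does not close the gap, because a need for ICU care is not the same as arrival there.

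A second reply is that the article condenses a fuller protocol, which might name another source. It might. The point does not rest on missing detail, though: the article says how the list is compiled and what it is used for, and a count made that way does not match the operating room definition of eligibility.

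Three stronger readings are tempting and are not supported.

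- *The overstatement is known to be several points, perhaps 7 or 8.* A reader might treat the yearly institutional count as already ICU-screened and suppose that 15% of all eligible patients are missing. Then 90 / 0.85 = 105.9 and 46 / 105.9 = 43.4%, against 51.1%, a gap of 7.7 points. But the Sample size section does not say that its count comes from ICU screening. Because enrolled patients cannot be missed, the whole loss also falls on the rest: 15.9 of 59.9, or 26.5% of non-enrolled candidates, would have to die before the ICU. Even 5% of all eligible implies 4.7 of 48.7, or 9.7%. Nothing in the documents supports such rates.
- *Numerator and denominator use different populations by definition.* Both rest on the same inclusion and exclusion criteria. What differs is how the non-enrolled are ascertained.
- *The trial conceals selection of less severe cases.* The article provides for reasons for non-enrolment to be recorded for every candidate identified. Some candidates may go unidentified, but selection by severity is conjecture.

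**Conclusion.** The concern holds as a one-sided gap in ascertainment. Following the stated screening method, eligible non-enrolled patients who die before ICU arrival are left out while enrolled ones are kept. The feasibility ratio can therefore only be overstated by this route, and the CONSORT screening counts can be incomplete.

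The direction follows from the text. The size does not: the range of 0 to about 5.6 points rests on the assumed loss of 0 to 20% and on reading the institutional caseload as the eligible population. If no such death occurs, the error is zero.

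This is a minor improvement. It touches one secondary endpoint and the screening counts. A reader might infer that the treatment comparison is also biased, but patients missed by the screen were never randomised, so neither that comparison nor the primary IL-6 endpoint is affected.

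**What to change.** In the section on eligible, non-randomized patients:

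1. Supplement the daily ICU screen with a periodic match by the coordinators against operating room records of damage control laparotomies. The article does not describe such records, so their availability is an assumption. The Trial status section reports 37 patients already enrolled, so the match should reach back to the first enrolment.
2. Count as eligible only patients who meet all inclusion criteria, including the ICU requirement, and none of the exclusion criteria. A denominator of all damage control laparotomies would bring in ineligible patients and push the ratio downward.
3. Show eligible patients who died before ICU arrival on a separate CONSORT line.
4. Use this one list as the denominator of the feasibility endpoint.

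If matching is not practicable, restrict the ratio to patients who reach the ICU, in both numerator and denominator, and say so where the endpoint is defined.

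The cost is a small amount of coordinator time and possibly a slightly lower feasibility figure. Randomisation, sampling and the IL-6 analysis do not change.
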